|--|--------------------------------------------------------------------------------------------------------------------------------------------------------------------------------------------------------------------------------------------------------------------------------------------------------------------------------------------------------------------------------------------------------------------------------------------------------------------------------------------------------------------------------------------------------------------------------------------------------------------------------------------------------------------------------------------------------------------------------------------------------------------------------------------------------------------------------------------------------------------------------------------------------------------------------------------------------------------------------------------------------------------------------------------------------------------------------------------------------------------------------------------------------------------------------------------------------------------------------------------------------------------------------------------------------------------------------------------------------------------------------------------------------------------------------------------------------------------------------------------------------------------------------------------------------------------------------------------------------------------------------------------------------------------------------------|

|                         |                                                                                                                                                                                                                                                                                                                                                                                                                                                                                                                                                                                                                                                                                                                                                                                                                                                                                                                                                                                                                                                                                                                                                                                                                                                                                       |
|-------------------------|---------------------------------------------------------------------------------------------------------------------------------------------------------------------------------------------------------------------------------------------------------------------------------------------------------------------------------------------------------------------------------------------------------------------------------------------------------------------------------------------------------------------------------------------------------------------------------------------------------------------------------------------------------------------------------------------------------------------------------------------------------------------------------------------------------------------------------------------------------------------------------------------------------------------------------------------------------------------------------------------------------------------------------------------------------------------------------------------------------------------------------------------------------------------------------------------------------------------------------------------------------------------------------------|
|                         | 
 
- Individuals who do not accept to participate in the study and / or whose guardians do not agree to participate in the study.
 
- Hospitalized patients
 
- Patients with severe conditions requiring hospitalization
 
- Pre-vaccination positive COVID-19 serology (IgG or neutralization antibodies).
 
                                                                                                                                                                                                                                                                                                                                                                                                                                                                                                                                                                                                                                                                                                                                                                                                                                                                                                      |
| RELEVANT METHODS | 
ARD patients and controls will be vaccinated with the vaccine against COVID-19 by HCFMUSP.
 
The vaccination protocol will consist of two doses of the COVID-19 vaccine for patients and controls, in addition to the collection of a blood sample on the day of the 1st vaccine dose (D0), on the day of the 2nd vaccine dose (28 days after first dose) and 40 days after the second dose of the vaccine. An additional (third) dose will be given 6 months after the second dose (D210) and immunogenicity will be assessed 30 days later (D240). Blood collection will also be performed at D210 prior to vaccination (3rd dose) to assess humoral response decay.
 
The serum obtained during collection will be stored in a -70°C freezer for testing for immunogenicity.
 
Immunogenicity will be assessed using the seroconversion rates of total IgG antibodies against S1 and S2 antigens and neutralizing antibodies to SARS-CoV-2 on the day of the 2nd dose and 40 days after the 2nd dose, using the 2-dose vaccine schedule is 28 days apart. Additionally, immunogenicity will be assessed prior to the third dose vaccination, 6 months after the second dose, and 30 days after the third dose vaccine dose (6 months after the second dose).
 |
| SAFETY           | 
Healthy patients and controls will be advised of the possible side effects of the vaccine. In addition, patients and controls will be
                                                                                                                                                                                                                                                                                                                                                                                                                                                                                                                                                                                                                                                                                                                                                                                                                                                                                                                                                                                                                                                                                                                                          |

|  |                                                                                                                                                                                                                                                                                                                                                                                                                                                                                                                                                                                                                                                                                                                                                                                                                                                                                                                                                                                                                                                                                                                                                                                                                                                                                                                                                                                                                                                                                                                                                                                                                                                                                                                                                                                                                        |
|--|------------------------------------------------------------------------------------------------------------------------------------------------------------------------------------------------------------------------------------------------------------------------------------------------------------------------------------------------------------------------------------------------------------------------------------------------------------------------------------------------------------------------------------------------------------------------------------------------------------------------------------------------------------------------------------------------------------------------------------------------------------------------------------------------------------------------------------------------------------------------------------------------------------------------------------------------------------------------------------------------------------------------------------------------------------------------------------------------------------------------------------------------------------------------------------------------------------------------------------------------------------------------------------------------------------------------------------------------------------------------------------------------------------------------------------------------------------------------------------------------------------------------------------------------------------------------------------------------------------------------------------------------------------------------------------------------------------------------------------------------------------------------------------------------------------------------|
|  | 
instructed to note in a standard diary the changes that occur in the period, such as:
 
Local reactions: pruritus, local pain, erythema, induration at the vaccine site,
 
Systemic reactions: tiredness, fatigue, headache, nausea, diarrhea, fever, chills, myalgia, arthralgia and diarrhea, signs of airway infections (cough, sputum, sore throat, ear pain or discharge, nasal congestion or expectoration, dyspnoea, sneezing), fever (axillary temperature > 37.8° C), itchy skin, rash, vertigo, abdominal pain, drowsiness, malaise, flushing, extremity pain / discomfort, back pain, edema, inappetence.
 
In addition, the need for medical care, hospitalizations, severity of infections, sick days, absenteeism at work and treatment received will be raised, regarding a clinical condition compatible with COVID-19.
 
The standardized diary of adverse events will be evaluated by the researchers 28 days after the first dose of vaccine and 40 days after the second dose. The diary includes guidance for telephone communication of any events that require hospital care. If tertiary care is required, the participant will be transferred to our University hospital (Hospital das Clínicas FMUSP). Serious adverse events will be defined as those that result in hospitalization or death. They will be reported to the National Ethics Committee (CONEP) within 24 hours.
 
Surveillance will be maintained for new cases of COVID-19 through weekly WhatsApp messages. For patients who present symptoms compatible with COVID-19 infection after vaccination, according to the recommended routine for monitoring immunosuppressed patients with a suspicious condition, a nasal swab will be collected to perform PCR for COVID, with sequencing
 |
|--|------------------------------------------------------------------------------------------------------------------------------------------------------------------------------------------------------------------------------------------------------------------------------------------------------------------------------------------------------------------------------------------------------------------------------------------------------------------------------------------------------------------------------------------------------------------------------------------------------------------------------------------------------------------------------------------------------------------------------------------------------------------------------------------------------------------------------------------------------------------------------------------------------------------------------------------------------------------------------------------------------------------------------------------------------------------------------------------------------------------------------------------------------------------------------------------------------------------------------------------------------------------------------------------------------------------------------------------------------------------------------------------------------------------------------------------------------------------------------------------------------------------------------------------------------------------------------------------------------------------------------------------------------------------------------------------------------------------------------------------------------------------------------------------------------------------------|

|  |                                                                                                                                                                                                                                                                                                                                                                                                                                                                                                                                                                                                                                                                                                                                                                                                                                                                                                                                                                                                                                                                                                                                                                                                                                                                                                                                                                                                                                                                                                                                                                                                                                                                                                                                                                                                                                                                                              |
|--|----------------------------------------------------------------------------------------------------------------------------------------------------------------------------------------------------------------------------------------------------------------------------------------------------------------------------------------------------------------------------------------------------------------------------------------------------------------------------------------------------------------------------------------------------------------------------------------------------------------------------------------------------------------------------------------------------------------------------------------------------------------------------------------------------------------------------------------------------------------------------------------------------------------------------------------------------------------------------------------------------------------------------------------------------------------------------------------------------------------------------------------------------------------------------------------------------------------------------------------------------------------------------------------------------------------------------------------------------------------------------------------------------------------------------------------------------------------------------------------------------------------------------------------------------------------------------------------------------------------------------------------------------------------------------------------------------------------------------------------------------------------------------------------------------------------------------------------------------------------------------------------------|
|  | 
for mutant strains in positive cases. for a period of up to 12 months after the 2nd dose of the vaccine. Positive samples will be sequenced by the protocol established at IMT-FMUSP (1) using the MinION platform (Oxford Nanopore Technologies, UK). The extracted RNA is converted into cDNA using the SuperScript IV First-Strand Synthesis System (Thermo Fisher Scientific, USA) and amplification of the complete genome using the Multiplex PCR protocol - version 3, described by Quick 2020 (2). The amplified samples are purified using 1x Ampure XP beads (Beckman Coulter, United Kingdom) and 70% alcohol solution twice. Amplicons are quantified with Qubit dsDNA High Sensitivity Assay Kit fluorophore and assayed in the Qubit 3.0 instrument (Life Technologies, USA (ThermoFisher) as recommended by the manufacturer. Amplicons are normalized to 240 ng and identified with barcodes. the following EXP-NBD104 (1-12) and EXP-NBD114 Native Barcoding Kits (Oxford Nanopore Technologies, UK) and Ligation Sequencing kit (ONT, SQK-LSK109) are used according to protocol (2). The final library is then loaded into the flowcell R9.4.1 and sequenced using the MinION platform (Oxford Nanopore Technologies - ONT) .The programs MinKNOW (version 19.10.1) and RAMPART are used to monitor the sequencing run in real time (https://artic.network/rampart)
 
After the end of the race, the fast5 files are subjected to base calls and separation of the barcodes (basecalled and demultiplexed) using the Guppy software, version 2.2.7 (Oxford Nanopore Technologies, UK). To obtain the consensus sequences, the fastq5 files are mapped against the reference genome of SARS-CoV-2 isolate Wuhan-Hu 1 (GenBank accession number MN908947) using the program minimap2 (version 2.28.0) and SamTools.
 |
|--|----------------------------------------------------------------------------------------------------------------------------------------------------------------------------------------------------------------------------------------------------------------------------------------------------------------------------------------------------------------------------------------------------------------------------------------------------------------------------------------------------------------------------------------------------------------------------------------------------------------------------------------------------------------------------------------------------------------------------------------------------------------------------------------------------------------------------------------------------------------------------------------------------------------------------------------------------------------------------------------------------------------------------------------------------------------------------------------------------------------------------------------------------------------------------------------------------------------------------------------------------------------------------------------------------------------------------------------------------------------------------------------------------------------------------------------------------------------------------------------------------------------------------------------------------------------------------------------------------------------------------------------------------------------------------------------------------------------------------------------------------------------------------------------------------------------------------------------------------------------------------------------------|

|                             |                                                                                                                                                                                                                                                                                                                                                                                                                                                                                                                                                                |
|-----------------------------|----------------------------------------------------------------------------------------------------------------------------------------------------------------------------------------------------------------------------------------------------------------------------------------------------------------------------------------------------------------------------------------------------------------------------------------------------------------------------------------------------------------------------------------------------------------|
|                             | Bioinformatics analyzes will follow the protocols described by the research group ARTIC ( https://artic.network/ncov-2019 ).                                                                                                                                                                                                                                                                                                                                                                                     |
| STATISTICAL ANALYSIS | The results will be presented as mean $\pm$ standard deviation (SD) or median for continuous variables and percentage for categorical variables. Data for continuous variables will be compared using Student's t-test or Mann-Whitney to assess differences in immunogenicity (serology) between patients with rheumatic diseases versus healthy controls. Differences between categorical variables (safety and effectiveness) will be assessed using the chi-square or Fisher's exact tests. Statistical significance will be established with $p < 0.05$ . |

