| OUTCOMES    | 
Primary Outcome Measure:
 
 
1. Immunogenicity of CoronaVac in a cohort of ARD patients compared with age- and sex-matched controls without these conditions: 
 
- Seroconversion rate of anti-SARS-Cov-2 IgG antibodies
 
- Presence of <math>\geq 30\%</math> of neutralizing activity of SARS-CoV-2 antibodies
 
 
 
2. Safety of CoronaVac in ARD patients compared with controls without these conditions
 
3. Immunogenicity of CoronaVac in a cohort of ARD patients compared with age- and sex-matched controls without these conditions 6 months after the second vaccine dose.
 
4. Immunogenicity of an additional 4th dose of a mRNA (BNT162b2) heterologous SARS-CoV-2 vaccine in poor/non-responders ARD patients previously vaccinated with 3rd of a SARS-CoV-2 inactivated vaccine.
 
 |
| SAMPLE SIZE | 
 
1. AUTOIMMUNE RHEUMATIC DISEASES (ARD) PATIENTS
 The sample size calculation was based on the previous 15% reduction of seroconversion rate after primo vaccination with the 2009 non-adjuvanted influenza A/H1N1 vaccine in a large cohort of ARD patients. Expecting seroconversion rates of 63% in the ARD patient's cohort and 78% in the control group, considering an alpha error of 5% and power of 80%, in 5 : 1 ratio in order to include more ARD patients, the minimum sample required would
 
                                                                                                                                                                                                                                                                                                                                                                                   |

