|                     | 
be 445 ARD patients and 89 healthy subjects, sex-matched and with similar ages. Expecting a higher SC rate of 98% for this vaccine, such sample size had a power greater than 99% to detect a 15% reduction in SC of ARD patients. Due to the peak of pandemics ongoing in Brazil during the vaccination period, we invited more patients and controls, expecting a high incidence of previously infected people and a high rate of infections.
 
A sample was calculated for patients with other rare rheumatological diseases, grouped into five diseases (systemic scleroderma, dermatomyositis/myositis, primary Sjogren's syndrome, systemic vasculitis and primary antiphospholipid antibody syndrome) being followed up in Rheumatology outpatient clinic (HCFMUSP). For the calculation, a seroconversion ratio of <math>p_1 = 50\%</math> is assumed for each disease and <math>p_2 = 74.25\%</math> as the average seroconversion of healthy controls. The sample size for each rare disease was 50, thus 250 being the number of patients with other diseases.
 
2. CONTROL GROUP: 271 healthy controls matched for age and sex will be included according to the need for controls for lupus (<math>n = 74</math>), rheumatoid arthritis (<math>n = 61</math>) and ankylosing spondylitis / psoriatic arthritis (<math>n = 136</math>) will be selected to receive the vaccine at HCFMUSP.
 |

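### The diary's systemic reactions include ordinary rheumatic symptoms, with no pre-vaccination record, so the patient-control comparison of systemic events is confounded against patients

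*Protocol*

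**What the plan says.** The Outcomes section of the protocol lists, as the second primary outcome measure, "Safety of CoronaVac in ARD patients compared with controls without these conditions".

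The Safety section gives the instrument. Patients and controls are "instructed to note in a standard diary the changes that occur in the period, such as" the items that follow. Local reactions at the vaccine site come first, then a separate list: "Systemic reactions: tiredness, fatigue, headache, nausea, diarrhea, fever, chills, myalgia, arthralgia and diarrhea, signs of airway infections". That list ends with "flushing, extremity pain / discomfort, back pain, edema, inappetence". The diary "will be evaluated by the researchers 28 days after the first dose of vaccine and 40 days after the second dose". Serious adverse events are defined separately, by hospitalization or death.

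Under Relevant Methods, the only procedure named for the day of the first dose, besides vaccination, is a blood sample. Under Statistical Analysis, categorical safety variables are compared by chi-square or Fisher's exact test, with no adjustment mentioned.

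On COVID-19, the Sample Size section explains the wider recruitment as "expecting a high incidence of previously infected people and a high rate of infections". The Safety section adds weekly messages and a PCR swab when symptoms appear.

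**The concern.** Joint pain, muscle pain, fatigue, and back and limb pain are ordinary features of rheumatoid arthritis, spondyloarthritis, lupus, myositis and related diseases. All of them fall under the diary's systemic heading. The controls are chosen because they do not have these diseases, and matching on age and sex does not give them the same background rate of such symptoms. There is no unvaccinated ARD group, and no within-patient record from before the first dose. A difference in systemic events between the groups therefore mixes any difference in vaccine reactions with the background of the disease, and the two cannot be separated afterwards.

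The background effect pushes in one direction, towards more events in patients. A larger sample makes a false difference more certain; it does not remove it. The stake is a primary-outcome result suggesting that the vaccine is tolerated less well by the group whose vaccination the study is meant to inform.

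**Working it through.** **The plan's own figure.** The only sample size with a full set of inputs is for seroconversion: 63% versus 78%, two-sided alpha 5%, power 80%, five patients per control. The pooled-variance formula for two proportions, without continuity correction, uses an average rate of (0.78 + 5 × 0.63)/6 = 0.655:

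n(controls) = [1.960 × √(0.655 × 0.345 × 1.2) + 0.842 × √(0.78 × 0.22 + 0.63 × 0.37/5)]² / 0.15² = 88.8, so 89 controls and 5 × 89 = 445 patients.

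This agrees with the protocol. No event rate or power is given for safety, so everything below is illustrative.

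**Illustration 1: accumulating background symptoms, no vaccine effect at all.**
- Assumed weekly chance of newly noting a listed musculoskeletal symptom: 2% to 5% in patients, 1% in controls. These rates are not in the document.
- Assumed counting period: 28 + 40 = 68 days, that is, all entries up to each evaluation.
- Formula: 1 − (1 − w)^(68/7).

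| Weekly rate w | Over 68 days |
|---|---|
| 1% (controls) | 9.3% |
| 2% (patients, low) | 17.8% |
| 5% (patients, high) | 39.2% |

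The false difference is 17.8 − 9.3 = 8.5 points at the low end and 39.2 − 9.3 = 29.9 at the high end, so about 9 to 30 points.

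Chi-square test at 445 versus 89:
- Low end: pooled rate 0.164, standard error √(0.164 × 0.836 × (1/445 + 1/89)) = 0.043, z = 0.085/0.043 = 1.98. The p-value is about 0.04 to 0.07, depending on rounding to whole participants and on continuity correction. This is borderline.
- High end: pooled rate 0.343, standard error 0.055, z = 5.4, p about 10⁻⁷ or smaller.

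With the 271 controls planned in the Control Group paragraph instead of 89, the low end falls to p of about 0.002 to 0.003.

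**Illustration 2: the same true reaction rate in both groups, plus background.** Assume 20% true reactions in each group and a 5% background in controls. With background b, P(event) = 1 − (1 − 0.20)(1 − b), which is 24% in controls. At 445 versus 89, the chance of p < 0.05 with more events in patients is:

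| Patient background | Patient event rate | Chance of a false excess |
|---|---|---|
| 10% | 28% | 11% |
| 15% | 32% | 31% |
| 20% | 36% | 60% |
| 30% | 44% | 96% |

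If both backgrounds are 5%, the test keeps its nominal 5% error rate. The problem comes from the excess of background in patients, not from background as such.

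**What a shorter window does alone.** Counting only 7 days after each dose gives 1 − (1 − w)²: 2.0% in controls and 4.0% to 9.8% in patients. The false difference shrinks to about 2 to 8 points but does not vanish.

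**COVID-19.** Airway signs and fever are on the same list, and no rule removes PCR-positive episodes from it. If infection is equally frequent and equally recorded in both groups, it adds events to both, as in the equal-background case above, and creates no false difference.

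**The case against.** The case on the other side is substantial, and much of it stands.

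- **The diary asks for changes.** Stable long-standing symptoms may therefore go unrecorded. This is fair, but there is no recorded reference state to check against, and a flare weeks after a dose is still a change.
- **The protocol does not call these events vaccine harm.** A reader might infer from the heading over the list that disease symptoms will definitely be scored as caused by the vaccine. The text does not go that far. It also calls the instrument a diary of adverse events, names the outcome safety, and states no rule on causality and no composite endpoint. The supportable statement is that such symptoms can be counted.
- **Days 28 and 40 are evaluation dates.** The period covered by the diary is not defined, so the 68-day window is an assumption. It is the natural one, since no shorter window is stated.
- **COVID-19 need not hurt patients.** A reader might take the airway symptoms as a second bias against patients. The document does not predict more infections in patients than in controls, and surveillance could identify episodes. The swab sentence mentions only patients, so recording might differ, but that alone does not establish a bias.
- **Windows and PCR rules may sit in an analysis plan that is not shown.** Agreed; their absence alone is no fault. An analysis plan cannot, however, recreate a pre-vaccination symptom record that was never collected.
- **The assumed rates produce the result.** They do, and other rates would give other differences.
- **A single baseline record shares the weakness.** A patient whose disease fluctuates can be worse than baseline by chance. This stands as a limit of the remedy.

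**Conclusion.** The concern holds for the systemic part of the second primary outcome. With disease-type symptoms on the list, no pre-vaccination record, disease-free controls and an unadjusted test, the comparison of systemic events is confounded against patients.

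The size is unknown. Under the assumed weekly rates and a 68-day count it is 9 to 30 points. A modest background excess can be enough for a significant result, but significance is not assured: the low case is borderline at 445 versus 89.

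It would go too far to conclude that the whole safety outcome is uninterpretable. Vaccine-site reactions and serious events are recorded separately and are largely unaffected. COVID-19 symptoms may be misclassified as reactions in either group, but they distort the contrast only if infection or its recording differs between groups.

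**What to change.** On the day of the first dose, before vaccination, and again before the second dose, have every participant complete the diary's symptom list for a short preceding period. Base the patient-control comparison of systemic reactions on symptoms that are new or worse than that record, with onset in one prespecified short window after each dose, identical in both groups; 7 days is one example. Report later entries in a separate table, and report PCR-positive COVID-19 episodes as COVID-19. The baseline record belongs in the protocol; the window and the PCR rule could be set in the analysis plan.

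The cost is one extra page at two existing visits and a derivation from onset dates. Later-onset reactions leave the main comparison, though they are still reported. Some confounding from fluctuating disease will remain and should be acknowledged when the results are interpreted.
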